**Methods:**

We will conduct an exploratory non-randomised controlled clinical trial with accompanying process and cost evaluation with three intervention and three control wards at one university hospital. The person-centred care intervention consists of 14 components reflecting the activities of expanded practice nurses within the interprofessional team on the intervention wards. The intervention will be implemented over a six-month period and compared with optimised care on the control wards. We will include people aged 65 years and older with existing cognitive impairment and/or at risk of delirium. The estimated sample size is 720 participants. The primary outcome is length of hospital stay. Secondary outcomes include prevalence of delirium, prevalence of agitation, sleep quality, and person-centred care. We will collect patient level data at six time points (t_1_ admission, t_2_ day 3, t_3_ day 7, t_4_ day 14, t_5_ discharge, t_6_ 30 days after discharge). For secondary outcomes at staff level, we will collect data before and after the intervention period. The process evaluation will examine degree and quality of implementation, mechanisms of change, and the context of the complex intervention. The economic evaluation will focus on costs from the hospital’s perspective.

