#### Assignment of intervention

Allocation of wards as intervention or control ward was based on ward managers’ decision to participate in the intervention. Participants’ assignment will be determined by their wards’ assignment.

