#### Sample size

The sample size is based on a recent retrospective cohort study which investigates the length of hospital stay in older people living with dementia by matching people without dementia in Germany [63]. We assume a mean reduction in the length of hospital stay of three days (intervention vs. control). With a standard deviation of 18 vs. 16 days, an intraclass correlation coefficient of 0.05 [64], and three clusters per treatment group with 120 people with cognitive impairment each, the adjusted two-sample t-test will reach a power of 81.5% at one-sided significance level of 50% [65]. Thus, this exploratory trial will be sufficiently powered to show the hypothesized direction of effect only.

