#### Data analysis

Statistical analysis is according to intention-to-treat (no exclusions). We will evaluate the primary outcome length of hospital stay by the stratified log-rank test (death is censored). Nota bene, the stratified log-rank test has very similar characteristics as the stratified van-Elteren rank-sum test and is available in many (statistical) software packages. We will use a propensity score approach (PSA) to balance individual characteristics between participants in intervention and control groups. In the multivariable logistic regression for PSA, we will use the independent variables age, gender, severity of cognitive impairment, Charlson Comorbidity Index, admission type, expected admission diagnosis-related or ward-related length of stay, and hospitalisations during the last 7 days [66, 67] as these variables are likely to be associated with outcome. Moreover, we will carefully monitor mortality in both arms, although we do not expect any difference. We will evaluate secondary outcome measures by (generalised) mixed models for repeated measures over time. If feasible, we will take outcome measures (particularly those reported by people with cognitive impairment) over the course of hospital stay. Thus, we may need to evaluate the outcome trajectories by random coefficient models. We will categorise and compare safety outcomes by frequency, relatedness, seriousness, and severity. Moreover, we will summarise variables by mean, standard deviation, and percentiles (0, 25, 50, 75, and 100) respectively by absolute and relative frequencies (percentage). Due to the small number of clusters, we will at least account for them in a fixed effect analysis. Though we will attempt to estimate corresponding random effects (e.g., to derive intraclass correlation), this seems prone to bias.

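### Accounting for wards by fixed effects cannot deliver a valid test of treatment on length of stay, because every ward lies wholly in one arm

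*Protocol article*

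**What the plan says.** All references are to the protocol article, under Evaluation of effects.

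- **Assignment of intervention:** "Participants’ assignment will be determined by their wards’ assignment". Ward managers decided whether their ward took the intervention.
- **Sample size:** the calculation uses "three clusters per treatment group with 120 people with cognitive impairment each" and "an intraclass correlation coefficient of 0.05", with a difference of three days and standard deviations of 18 and 16 days. It reports 81.5% power for an adjusted two-sample t-test at a one-sided 50% level and says that this supports a statement on direction only.
- **Table 1:** length of stay is recorded once per patient, at discharge.
- **Data analysis, primary outcome:** length of stay is evaluated "by the stratified log-rank test (death is censored"). The strata are not named. A propensity score approach is to balance individual characteristics.
- **Data analysis, clusters:** "Due to the small number of clusters, we will at least account for them in a fixed effect analysis". The next sentence adds: "Though we will attempt to estimate corresponding random effects (e.g., to derive intraclass correlation), this seems prone to bias".

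**The concern.** A ward fixed effect uses up all the information on differences between wards. In this design the treatment comparison consists only of differences between wards. The committed minimum analysis therefore removes the comparison it is meant to support, or keeps it with a standard error that reflects only variation among patients.

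Either way, a chance or pre-existing difference between two sets of three self-selected wards cannot be told apart from an effect of the intervention. The Objectives include testing clinical effectiveness, and the Discussion expects the results to inform management and policy decisions. Falsely precise p-values and intervals would therefore be used.

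**Working it through.** **Inputs (Sample size section).** k = 3 wards per arm; m = 120 patients per ward, so 360 per arm and 720 in total; ICC = 0.05; SDs 18 and 16 days; difference 3 days; one-sided level 50%.

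**1. The protocol's own power figure.**
- Design effect = 1 + (120 − 1) × 0.05 = 6.95.
- SE = √[(18² + 16²)/360 × 6.95] = √[580/360 × 6.95] = 3.35 days.
- 3/3.35 = 0.897. At a one-sided 50% level the critical value is zero, so power = Φ(0.897) = 81.5%.

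The stated figure reproduces. The sample size calculation thus carries between-ward variance.

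**2. Is treatment estimable alongside ward fixed effects?** Six ward indicators have rank 6. Adding the treatment indicator gives seven columns, still of rank 6. Treatment is the sum of three ward indicators, so for a once-measured outcome its effect is aliased.

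**3. Log-rank test stratified by ward.** Each stratum holds one arm only. At every event time the expected number of discharges in that arm equals the observed number. So O − E = 0 and the variance is 0 in every stratum, and the statistic is 0/0. A run on generated data returned exactly 0 and 0.

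**4. The other fixed-effect readings.**
- *Strata that are not wards (e.g. propensity strata), with patients treated as independent.* For a difference in means, SE = √(580/360) = 1.27 days. The ratio to the clustered SE is √6.95 = 2.64.
- *Treatment as a contrast of fixed ward effects.* Only within-ward variance remains, and the ratio is √[1 + 120 × 0.05/0.95] = 2.70.

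**5. What that does to a test.** The article states no 5% level, so this step assumes a nominal two-sided 5% test. With wards ignored, the true false-positive rate is 2 × [1 − Φ(1.96/√DE)].

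| ICC | Design effect | False-positive rate |
|---|---|---|
| 0.01 | 2.19 | 18.5% |
| 0.02 | 3.38 | 28.6% |
| 0.05 (protocol) | 6.95 | 45.7% |
| 0.10 | 12.9 | 58.5% |

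With treatment as a contrast of fixed ward effects, the rate at ICC 0.05 is 46.9%. In 20,000 simulated null trials with normal data the rates were 46.2% (wards ignored) and 47.0% (fixed ward effects).

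**6. The only level the article states, one-sided 50%.** The false-positive rate is 1 − Φ(0) = 50% whatever the design effect (simulated 49.7%). There is no inflation at that level.

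**7. A ward-level comparison.** A t-test on six ward means (4 df) rejected 5.4% of simulated null trials at a nominal two-sided 5%. With the protocol's inputs its power is 81.5% at one-sided 50%, 18.6% at one-sided 5% and 10.4% at two-sided 5%. The 95% half-width is 2.776 × 3.35 = 9.3 days.

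**The case against.** Five points can be made for the plan.

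- **The trial claims direction only.** This stands as far as it goes. At one-sided 50% only the sign of the difference counts. With equal ward sizes a patient-level and a ward-level comparison of means have the same sign, so the 81.5% is the same for both. A reader might infer that the trial has a 46% false-positive rate, or that the stated power is wrong because the analysis uses another variance. The article supports neither: the first needs a test level it never sets, and the second fails for a comparison of means at the level it does set. What remains is that an aliased effect gives no direction at all, and that any reported p-value or interval would be too precise.
- **Random effects will also be attempted.** They will, and such a model would carry between-ward variance. But the article itself calls the attempt prone to bias and offers deriving the ICC as its example use. The commitment is to the fixed-effect analysis.
- **The strata are unnamed and may be propensity strata.** This is plausible, and naming them can be left to the analysis plan. It avoids the undefined test but leads to step 4 of the working, where patients count as independent. The propensity score balances individual characteristics and does not remove variation between wards.
- **Ward fixed effects do not remove treatment from every model.** Correct. For outcomes measured repeatedly, such as delirium from admission to discharge or the staff scales before and after, arm-by-time effects remain estimable. The aliasing is confined to once-measured outcomes: length of stay and, among secondary outcomes, for example the quality-of-life scales and the individualised care scale at discharge.
- **The study is exploratory, and the Discussion admits a high risk of selection bias.** True, but that limitation concerns baseline differences between groups. It does not address the between-ward variance missing from the standard error.

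**Conclusion.** The point holds for outcomes measured once per patient, and so for the primary outcome. This is not a detail left to an analysis plan: the article names a method that its own design cannot support. Followed literally, it gives no treatment estimate. On the remaining fixed-effect readings, the standard error of a difference in means is too small by a factor of about 2.6 to 2.7.

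The structural part needs no assumption beyond three whole wards per arm. The factor rests on the protocol's ICC of 0.05, 120 patients per ward and the stated SDs, applied to means; the log-rank test itself was not recalculated. The 46% rests in addition on an assumed two-sided 5% level and should be quoted only with that condition and with its range of 19% to 59%. Neither the stated 81.5% power nor the error rate at one-sided 50% is called into question.

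**What to change.** Replace the fixed-effect sentence with a statement of how treatment is tested against variation between wards.

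- **Primary outcome:** compute a propensity-adjusted length-of-stay summary per ward, compare three with three by t-test on 4 df, and report the difference in days with its confidence interval. State how in-hospital deaths enter the ward summary, consistent with the planned censoring. Keep the log-rank analysis as descriptive.
- **Secondary outcomes measured once:** use ward-level summaries, or a random ward effect with small-sample degrees of freedom.
- **Repeated outcomes:** ward fixed effects may stay if the target is the arm-by-time effect, but ward-by-time variance must be allowed for.
- **Optional sensitivity check:** a permutation over the 20 possible allocations of six wards. It is coarse: the smallest two-sided p-value is 2/20 = 0.10, and it has no randomisation basis because the wards were not randomised.

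Cost: no new data are needed, but the primary test and the quantity it estimates change, so this is more than an edit of wording. The interval is wide, about ±9.3 days under the planning assumptions, and power at two-sided 5% is about 10%. Both agree with the protocol's own direction-only aim, and the 81.5% at one-sided 50% is retained.

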### Evaluation of processes

The process evaluation is based on a convergent parallel mixed-methods approach [68]. Theoretical foundations are the MRC guidance for process evaluations of complex interventions [69] and Grant’s framework on process evaluation for cluster-randomised trials [70]. For the design and conduct of the study, we developed a logic model that illustrates expected causal pathways of the ENROLE-acute intervention and potential moderating effects of relevant contextual factors (the logic model will be published as part of the intervention development). We used the logic model’s domains (implementation, mechanisms of change, and context) to organise all process variables in a predefined analysis-plan. Our purpose is that by evaluating processes before, during, and after the intervention period, observed effects can be interpreted in the light of how the complex intervention actually works. For an overview of domains, questions, data collection, participants, and time points, please see Table 2.

**Table 2 Tab2:** Overview of the evaluation of processes

**Domains**		**Questions**	**Data collection**	**Participants**	**Time points**^a^
Implementation	Recruitment of expanded practice nurses	How is recruitment done?	Documentation of recruitment	–	tp_0_
		Who is (not / no longer) participating?	Documentation of recruitment and retention	–	tp_0_, occasion-related
		Why do (potential) expanded practice nurses (not / no longer) participate?	Documentation of recruitment and retention	–	tp_0_, occasion-related
			Qualitative interviews on motivation and reasons for (non-)participation	(Potential) expanded practice nurses	Occasion-related
	Delivery to expanded practice nurses	What is delivered to the expanded practice nurses? Is it what the researchers intend?	Documentation of contact hours in training, internship, and coaching sessions	–	tp_1_, ongoing
			Review of training and coaching material and internship report	–	tp_1_, ongoing
			Review of coaching session protocols	–	tp_4_
	Recruitment of hospital wards	How is recruitment done?	Documentation of recruitment	–	tp_0_
		Who is (not / no longer) participating?	Documentation of recruitment and retention	–	tp_0_, occasion-related
		Why do wards (not / no longer) participate?	Documentation of recruitment and retention	–	tp_0_, occasion-related
			Qualitative interviews on motivation and reasons for (non-)participation	Ward managers	Occasion-related
	Delivery to interprofessional team members on hospital wards	What is delivered to the interprofessional team members? Is it what the researchers intend?	Documentation of participation in the kick-off event	–	tp_1_
			Review of the kick-off event and written information material	–	tp_1_
			Documentation of the expanded practice nurses’ activities in the interprofessional team in a logbook	Expanded practice nurses	Ongoing
			Review of coaching session protocols	–	tp_4_
	Recruitment of people with cognitive impairment and their relatives	How is recruitment done?	Documentation of recruitment	–	Ongoing
		Who is (not / no longer) participating?	Documentation of recruitment and retention	–	Ongoing
		Why do people with cognitive impairment and their relatives (not / no longer) participate?	Documentation of recruitment and retention	–	Ongoing
	Delivery to people with cognitive impairment and their relatives	What is delivered to the people with cognitive impairment and their relatives? Who is receiving? Is it what the researchers intend?	Documentation of the expanded practice nurses’ activities with people with cognitive impairment and their relatives in a logbook	Expanded practice nurses	Ongoing
			Review of coaching session protocols	–	tp_4_
			Qualitative dyad interviews on expanded practice nurses’ and interprofessional team members’ activities	People with cognitive impairment and their relatives	tp_3_
			Focus groups on expanded practice nurses’ and interprofessional team members’ activities	Expanded practice nurses, members of the interprofessional team	tp_4_
Mechanisms of change	Response of expanded practice nurses	Based on the Kirkpatrick model:	Reflection forms on satisfaction with and perceived usefulness of training, internship, and coaching sessions (1)	Expanded practice nurses	tp_1_
		How do expanded practice nurses react? (1) To what extent is there learning success? (2) To what extent can the learning be transferred to behaviour in everyday care? (3) To what extent are there results? (4)			
			Non-moderated, guided focus group on satisfaction with and perceived usefulness of training, internship, and coaching sessions as well as expectations for the intervention period (1, 3)	Expanded practice nurses	tp_1_
			Questionnaire on self-assessed knowledge (2)	Expanded practice nurses	tp_0_, tp_1_
			Documentation of the expanded practice nurses’ activities in a logbook (3)	Expanded practice nurses	Ongoing
			Review of coaching session protocols (3)	–	tp_4_
			Qualitative interviews on self-perceived skills and competences in core tasks (3, 4)	Expanded practice nurses	tp_4_
			Questionnaire on role understanding and collaboration (4)	Expanded practice nurses	tp_0_, tp_1_, tp_4_
	Response of interprofessional team members on hospital wards	How do interprofessional team members react? (1) To what extent do interprofessional team members accept what is delivered? (2) To what extent are there results? (3)	Reflection forms on satisfaction with and perceived usefulness of the kick-off event and written information material (1, 2)	Interprofessional team members	tp_1_, tp_4_
			Questionnaire on acceptability and role understanding of as well as collaboration with expanded practice nurses (1–3)	Interprofessional team members	tp_0_, tp_4_
			Questionnaire on attitudes towards and satisfaction with (person-centred) care for people with cognitive impairment (3)	Interprofessional team members	tp_0_, tp_4_
	Response of people with cognitive impairment and their relatives	How do people with cognitive impairment and their relatives react? (1) To what extent do people with cognitive impairment and their relatives accept what is delivered? (2) To what extent are there results? (3)	Qualitative dyad interviews on acceptability and role understanding of expanded practice nurses as well as satisfaction with expanded practice nurses’ and interprofessional team members’ activities (1–3)	People with cognitive impairment and their relatives	tp_3_
			Focus groups on patients’ acceptability and role understanding of expanded practice nurses as well as satisfaction with expanded practice nurses’ and interprofessional team members’ activities (1–3)	Expanded practice nurses, members of the interprofessional team	tp_4_
	Maintenance	To what extent are the processes maintained over time?	Documentation of contact hours in coaching sessions	–	Ongoing
			Documentation of the expanded practice nurses’ activities in the interprofessional team and with people with cognitive impairment and their relatives in a logbook	Expanded practice nurses	Ongoing
			Review of coaching session protocols	–	tp_4_
			Focus groups on expanded practice nurses’ and interprofessional team members’ activities	Expanded practice nurses, members of the interprofessional team	tp_4_
		What are the reasons for (lack of) maintenance?	Focus groups on staff intention and reasons for (lack of) expanded practice nurses’ and interprofessional team members’ activities	Expanded practice nurses, members of the interprofessional team	tp_4_
			Qualitative interviews on organisational intention and reasons for (lack of) expanded practice nurses’ and interprofessional team members’ activities	Ward managers	tp_4_
	Unintended consequences	Do unintended changes occur? What are the reasons for unintended changes?	Focus groups on unintended consequences of training, internship, and coaching sessions, kick-off event and written information material or expanded practice nurses’ and interprofessional team members’ activities	Expanded practice nurses, members of the interprofessional team	tp_4_
			Qualitative interviews on unintended consequences of training, internship, and coaching sessions, kick-off event and written information material or expanded practice nurses’ and interprofessional team members’ activities	Ward managers	tp_4_
			Qualitative dyad interviews on unintended consequences of expanded practice nurses’ and interprofessional team members’ activities	People with cognitive impairment and their relatives	tp_3_
Context	Micro level	What are the characteristics of the expanded practice nurses?	Questionnaire on sociodemographic, personal, and professional characteristics that may influence the intervention	Expanded practice nurses	tp_0_
		What are the characteristics of the interprofessional team members and ward managers?	Questionnaire on sociodemographic, personal, and professional characteristics that may influence the intervention	Members of the interprofessional team, ward managers	tp_2_
		What are the characteristics of the people with cognitive impairment and their relatives?	Patient records	–	tp_3_
			Qualitative dyad interviews on personal characteristics that may influence the intervention	People with cognitive impairment and their relatives	tp_3_
		To what extent do the characteristics act as barriers or facilitators?	Qualitative interviews on perceived barriers and facilitators	Expanded practice nurses, ward managers, nursing development unit	tp_4_
			Questionnaire on perceived barriers and facilitators	Members of the interprofessional team	tp_4_
			Qualitative dyad interviews on perceived barriers and facilitators	People with cognitive impairment and their relatives	tp_3_
	Meso level	What are the characteristics of the wards?	Questionnaire on ward characteristics that may influence the intervention	Ward managers	tp_4_
		What are the characteristics of the University Hospital Cologne?	Qualitative interviews on hospital characteristics that may influence the intervention	Nursing management, nursing development unit	tp_4_
		To what extent do the characteristics act as barriers or facilitators?	Qualitative interviews on perceived barriers and facilitators	Expanded practice nurses, ward managers, nursing management, nursing development unit	tp_4_
			Questionnaire on perceived barriers and facilitators	Members of the interprofessional team	tp_4_
	Macro level	What are the characteristics of the society?	Qualitative interviews on society characteristics that may influence the intervention	Nursing management, nursing development unit	tp_4_
		To what extent do the characteristics act as barriers or facilitators?	Qualitative interviews on perceived barriers and facilitators	Expanded practice nurses, nursing management, nursing development unit	tp_4_

^a^tp_0_ = before training, internship, and kick-off event; tp_1_ = after training, internship, and kick-off event; tp_2_ = start of the intervention period; tp_3_ = after transfer/discharge of people with cognitive impairment; tp_4_ = 6 months after the start of the intervention period

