**Fig. 2 Fig2:**
[figure not shown]
Intervention components

Each intervention ward receives two EPN, qualified at level six of the European Qualifications Framework (bachelor’s degree or equivalent further education) [33]. EPN are integrated into the ward's work schedule and have one day each every two weeks for additional activities.

We developed different implementation strategies to prepare the field. EPN received a 200-h training regarding fundamentals of caring for people with cognitive impairment, principles of PCC, and Advanced Practice Nursing in six modules. In addition, EPN gained knowledge of established expanded nursing models in other hospitals during a 10-day internship. During the intervention period, we accompany the EPN fortnightly in two-hour coaching sessions for reflection and implementation support. We also train the interprofessional team at the beginning of the intervention phase on PCC principles and Advanced Practice Nursing during a one-hour kick-off meeting and through written information.

Team members of control wards provide optimised care with knowledge acquired through a one-time half-hour session and written information on PCC.

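### Table 2 asks the expanded practice nurses to rate the coaching at tp1 only, when at most about one of roughly 13 sessions can have taken place

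*Protocol article*

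**What the plan says.** All places are in the protocol article.

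- **Delivery of coaching.** The Intervention section says: "During the intervention period, we accompany the EPN fortnightly in two-hour coaching sessions for reflection and implementation support". The Abstract gives the length of that period: "The intervention will be implemented over a six-month period".
- **Reaction instruments.** In Table 2, under mechanisms of change and the response of the EPN, code (1) stands for reaction. Two rows carry it. One is "Reflection forms on satisfaction with and perceived usefulness of training, internship, and coaching sessions (1"), the other is "Non-moderated, guided focus group on satisfaction with and perceived usefulness of training, internship, and coaching sessions as well as expectations for the intervention period", coded (1, 3). The time point for each is tp1 and nothing else.
- **Time points.** The footnote to Table 2 reads: "tp_1_ = after training, internship, and kick-off event; tp_2_ = start of the intervention period". The data collection section of the process evaluation lists them in the same order. The definition of tp1 names training, internship and kick-off, but not coaching.
- **Kick-off.** The Intervention section adds: "We also train the interprofessional team at the beginning of the intervention phase". The kick-off meeting that helps to define tp1 may therefore fall at the opening of the intervention phase, not clearly before it.

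**The concern.** A reaction measure asks people what they made of something they have received. Training and internship are complete at tp1, so asking about them then is sound. Coaching is different: it is the one EPN implementation strategy that the Intervention section describes as running through the intervention period. Asked at tp1, the coaching items would be left blank or would record an expectation that could later be reported as an experience.

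Objective (b) covers the degree and quality of implementation and the mechanisms of change, and the Discussion says the results should inform larger trials. Whether the nurses found the coaching worthwhile bears on whether to keep, shorten or change it. As scheduled, the reaction data cannot answer that.

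**Working it through.** The plan states no figure to reproduce here. The check compares the delivery schedule with the measurement schedule and counts sessions.

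**1. How much coaching is planned**

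- Inputs: six months (Abstract); one two-hour session every two weeks (Intervention). Assumption: six months is about 26 weeks.
- Sessions: 26 / 2 = 13.
- Hours: 13 × 2 = 26 for an EPN who attends every session.
- EPN: 3 intervention wards × 2 per ward = 6.

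**2. How much has happened at tp1**

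- If tp1 precedes tp2, as the order of the list implies: 0 of about 13 sessions.
- If the kick-off is held as the phase opens and tp1 follows directly: 0 to 1 of about 13, at most 1 / 13 = 7.7%.
- The focus group row supports an early tp1, because it also asks the EPN what they expect of the intervention period.

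**3. Whether another row fills the gap**

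The Table 2 rows that name coaching, or that question the EPN at tp4, are:

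| Source | Time point | What it gives |
|---|---|---|
| Reflection form, code (1) | tp1 | Reaction to training, internship, coaching |
| Non-moderated focus group, code (1, 3) | tp1 | The same, plus expectations |
| Contact hours | tp1, ongoing; ongoing under maintenance | Amount delivered |
| Review of training and coaching material | tp1, ongoing | Content delivered |
| Review of session protocols | tp4 | Coded (3), transfer, in the EPN response rows; a document review with no participants |
| EPN interviews on skills and competences | tp4 | Coded (3, 4) |
| Focus groups on activities, maintenance and its reasons | tp4 | What EPN and team do, and why it lasts or not |
| Focus groups on unintended consequences | tp4 | Names coaching and includes EPN, but asks about unintended effects |
| EPN interviews on barriers and facilitators | tp4 | Tied to characteristics of persons, wards, hospital and society |

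A separate row, ward manager interviews at tp4, also names coaching, again only for unintended consequences. Two EPN instruments carry the reaction code. Both are at tp1, and neither is at tp4 or ongoing.

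**4. Comparison within the same table**

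The interprofessional team's reflection forms, on a one-hour kick-off and written material, are scheduled at tp1 and again at tp4. The delivery row "Documentation of contact hours in training, internship, and coaching sessions" is marked tp1 and ongoing. Elsewhere, then, the table repeats a reaction measure at the end and recognises that coaching runs past tp1. The two EPN reaction rows do neither.

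**The case against.** The best reply is that this is a condensed table. One cell bundles three activities under one time point, and a missing tp4 or ongoing entry is at least as plausible as a deliberate plan to rate coaching before it starts. The article refers to a predefined analysis plan for process variables, and the interview guides are not shown. That is fair as to the cause. It does not remove the conflict: Table 2 and the Intervention section cannot both be followed as printed and still yield a rating of the coaching.

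Three stronger readings are tempting, and the documents do not support them.

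- **That exactly no coaching has occurred at tp1.** A reader might infer this from the order tp1, tp2. But tp1 has no stated upper limit, and the kick-off is placed at the opening of the intervention phase. The Intervention section also does not exclude an earlier session. The defensible count is about 0 to 1.
- **That the process evaluation learns nothing valid about coaching.** It will have contact hours, material, session protocols and tp4 focus groups that name coaching under unintended consequences. Open interviews with the same six EPN at tp4 may also bring it up. What is missing is narrower: a planned question on satisfaction and usefulness once coaching is under way.
- **That the level 3 question in the tp1 focus group is also misplaced, leaving transfer to everyday care unmeasured.** The ongoing logbook, the protocol review at tp4 and the EPN interviews at tp4 all carry code (3). A forward-looking question on transfer at tp1 is a reasonable baseline.

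It is also true that the matter concerns a few items from six nurses, to be analysed descriptively or by framework analysis.

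**Conclusion.** The point holds in this limited form. Both EPN reaction instruments ask about coaching at tp1 only, when about 0 to 1 of roughly 13 fortnightly sessions can have taken place, and no later row collects the EPN's satisfaction with the coaching or their view of its usefulness. The count assumes a 26-week period, a regular fortnightly rhythm, and coaching that begins with the intervention period as the Intervention section describes.

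The consequence is a gap in the process evaluation under objective (b). A reader should not extend it to the trial's results on length of stay, the safety outcomes or costs; none of them uses these items. The change is worth making because it is cheap and the data cannot be recovered properly once the EPN have dispersed.

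**What to change.** - Keep the training and internship items of the reflection form and the focus group at tp1.
- Collect the coaching satisfaction and usefulness items at tp4, either with the reflection form or as added questions in the EPN interviews already planned then. If coaching stays in the tp1 instruments, label those items as expectations.
- Reconcile Table 2 with the Intervention section. If some coaching does precede tp1, say so and state how much.

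The coding and timing of the level 3 sources can stay as they are.

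The cost is an edit to two rows of Table 2 and, at most, one short extra form for six EPN, or a few more interview questions. The drawback is that early sessions are rated from memory at tp4, up to about six months later.
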